### Primary and secondary outcomes

Primary outcome is the one-year pre- to post-implementation change in HbA1c.

Secondary outcomes are the one-year differences in cholesterol levels and systolic and diastolic blood pressure. A composite patient score and a composite process score are calculated representing the change in diabetes (process) control and associated cardiovascular risk [19]. The composite patient score consists of reaching the evidence-based targets for glycated hemoglobin, blood pressure (systolic and diastolic), and cholesterol. The process composite score consists of meeting the evidence-based targets of the number of blood pressure measurements, the number of laboratory results of HbA1c, cholesterol and micro-albuminuria, a prescription of statin (yes/no), if high cardiovascular risk a prescription of aspirin/clopidogrel (yes/no), if hypertension or nephropathy ACE inhibition/sartan (yes/no).

Outcomes that cannot be reliably detected from the electronic medical records such as smoking status, and feet and eye examinations are excluded from the composite scores, as well as outcomes in which family physicians’ influences are minimal (*e*.*g*., BMI, physical activity, etc.).

Outcomes of the composite scores with their respective targets are shown in Table 1. Recommendations and targets are based on the diabetes guidelines of Domus Medica [20] and the Belgian ‘Zorgtraject diabetes’ [21].

**Table 1 T1:** Variables included in the composite scores

***Variable***	***Process target***	***Maximum score per period****	***Clinical target***	***Maximum score per period***^**†**^
HbA1c	Quarterly	2	< 7%	1
Blood pressure	Quarterly	2	< 130/80 mm Hg	1
Cholesterol (LDL, HDL, Total)	Annual	1	LDL < 100 mg/dL	1
Microalbuminuria check	Annual	1		
A prescription of statin	Yes/no	1		
If high cardiovascular risk, a prescription of aspirin/clopidogrel	Yes/no	1		
If hypertension or nephropathy, ACE inhibition/sartan	Yes/no	1		
Total		9		3

*Maximum score for process composite per period = 9 (7 variables).

^†^ Maximum score for patient composite per period = 3 (3 variables).

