Each of the parameters in the composite scores is compared with their respective target. Each outcome that meets the target will be assigned one point. If all outcomes meet the targets, a maximum score of 3 points will be assigned to the patient composite score and a maximum score of 9 points will be assigned to the process composite score. If we cannot find any data about the process variable, we will assume that it did not happen. A variable that improves during the intervention period will be scored as +1; each variable that worsens will be scored as −1; and each variable that does not change will be scored as 0. As such, composite scores can be grouped into three categories: worsened, unchanged or improved.

The follow-up period will be 12 months. Outcomes will be collected at five points: before the start of the study, at 3 months, at 6 months, at 9 months and at 12 months, with the differences between pre- and post-implementation forming the outcome scores. A mean will be calculated for the intervention and control groups. The trial will be terminated at one of the interim analysis points when a mean difference of 0.3% might be reached for the primary outcome of HbA1c change.

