### Data analysis

Descriptive statistics will be provided regarding baseline variables of the patients and the family physicians. Intervention and control groups will be compared regarding baseline variables to evaluate the randomization. Linear mixed models will be used for continuous patient-level variables, with a random intercept to account for clustering of patients within physician practices. Logistic regression models based on generalized estimating equations (GEE) to account for clustering will be used for binary patient-level variables.

Differences between intervention and control groups regarding continuous outcome measures (change versus baseline in HbA1c, cholesterol levels, and blood pressure) will be assessed using linear mixed models (multilevel regression models) with random intercepts for physician practices and random intercepts for patients to account for repeated measurements over time. The primary fixed effect of interest will be the difference between intervention and control group, which will be tested at each time point (3 m, 6 m, 9 m and 12 m). If important differences in baseline characteristics are demonstrated between both groups, we will account for that by including the relevant variables in the model.

Differences between intervention and control groups regarding three-level composite scores (worsening, unchanged, improvement) will be assessed using random-effects proportional odds models, or, in case the proportional odds assumptions do not hold, baseline-category logits models, with random intercepts for physician practices and random intercepts for patients to account for repeated measurements over time. As with the analysis of continuous outcomes, differences between intervention and control groups will be tested at all time-points, and correction for imbalance in baseline characteristics will be applied if indicated.

To study the effect of the actual use of the EBMeDS system on the outcome measures, models similar to those described above will be used for analyzing the effect of intervention. However, they will now include a measure for the use of EBMeDS as the main explanatory variable, and will restrict analysis to the data obtained in the intervention group.

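### Changes in HbA1c and blood pressure are modelled from one pre-start extraction with no planned baseline adjustment, although earlier pre-start values are very likely within reach and could be prespecified as covariates

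*Protocol article*

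**What the plan says.** The Protocol article, Primary and secondary outcomes, sets the endpoint: "Primary outcome is the one-year pre- to post-implementation change in HbA1c". It gives the schedule: "Outcomes will be collected at five points: before the start of the study, at 3 months, at 6 months, at 9 months". The fifth and last collection comes one year after the start. How the outcomes are then formed is put this way: "with the differences between pre- and post-implementation forming the outcome scores". Data collection repeats the same five extraction times and says that the data come automatically from the electronic medical record.

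Data analysis names the modelled outcome as "change versus baseline in HbA1c, cholesterol levels, and blood pressure", with random intercepts for practice and patient and a test at each of the four follow-up times. Baseline covariates are conditional: "If important differences in baseline characteristics are demonstrated between both groups, we will account for that by including the relevant variables in the model".

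The process composite rests on "meeting the evidence-based targets of the number of blood pressure measurements, the number of laboratory results of HbA1c, cholesterol and micro-albuminuria". Table 1 gives HbA1c and blood pressure a quarterly target, worth at most 2 points each per period. Each variable is then scored as improved, unchanged or worsened.

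The article does not say which HbA1c counts as baseline when several precede the start, how long the pre-start period is, or whether earlier values are exported with their dates.

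**The concern.** A change score carries the whole error of its baseline. If that baseline rests on one reading, the same error enters the 3-, 6-, 9- and 12-month changes. The random patient intercept does not remove it, because it already sits inside the outcome. Adjusting for the baseline value reduces its influence, but the plan adjusts only after an observed imbalance, which is a reason unrelated to precision.

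The process score cannot be expressed as a change without counting HbA1c and blood pressure results from before the start. Those results come from the same record by the same automatic extraction, so reading their values as well as their number should be a small step. At stake is precision on the primary HbA1c comparison and on the blood pressure comparisons, not validity.

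**Working it through.** **1. The plan's own sample size** (inputs from Sample size: difference 0.3, SD of change 1.3, two-sided alpha 0.05/4 = 0.0125, power 80%, 10% withdrawal, 10 patients per cluster, ICC 0.047).
- Normal approximation: n = 2 × (1.3/0.3)² × (2.498 + 0.842)² ≈ 419 per arm. The exact t calculation gives 421.
- Withdrawal: 421 × 1.1 = 463.1, stated as 463.
- Design effect: 1 + 9 × 0.047 = 1.423, and 463 × 1.423 = 658.8, stated as 659.

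Both figures reproduce.

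**2. Assumptions for the gain.** The documents give no correlation between repeated HbA1c or blood pressure values and no number of pre-start results per patient. Below, the outcome is at 12 months, pre-start values are a quarter apart, variances are equal to 1, and every patient has k pre-start values.

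**3. Equal correlation r between all pairs.** Residual variance with k pre-start values as covariates is 1 − k r² / (1 + (k − 1) r).

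| r | k = 1 | k = 2 | k = 3 | cut, 2 v 1 | cut, 3 v 1 |
|---|---|---|---|---|---|
| 0.5 | 0.750 | 0.667 | 0.625 | 11% | 17% |
| 0.7 | 0.510 | 0.424 | 0.388 | 17% | 24% |

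With equal correlations, the last value plus the mean of the earlier ones gives the same results.

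**4. Mixed correlation** (stable share 0.3 to 0.5, decaying share 0.3 to 0.6, noise 0.1 to 0.2, summing to 1; quarterly decay 0.5 to 0.9). The cut relative to k = 1 is about 2% to 9% for k = 2 and 2% to 12% for k = 3.

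**5. Pure serial correlation (AR(1)).** Given the last value, earlier ones add nothing, so the cut is 0%.

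**6. Against the plan's raw change score.** Raw change has variance 2(1 − r). Adjusting for one baseline value multiplies it by (1 − r²) / (2(1 − r)) = (1 + r)/2, that is 0.75 at r = 0.5 and 0.85 at r = 0.7. Adding a second pre-start value takes these to 0.667/1.0 = 0.67 and 0.424/0.6 = 0.71. At r = 0.5, most of the total gain comes from adjusting at all; at r = 0.7 the two steps contribute about equally.

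**7. What shrinks the gain.** If practice-level variance does not fall, only the within-practice part benefits. With ICC 0.047 and 10 per cluster, that part is 0.953/1.423 = 0.67 of the variance that matters for the comparison. An 11% cut becomes about 7%, and 24% about 16% (taking 0.047 as the practice share in the adjusted model, which is an approximation). If only half the patients have a second value, the gain roughly halves.

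**8. An alternative that can lose precision.** Suppose the pre-start values are instead entered as extra repeated outcomes with a common mean in both arms. The plan's random-intercept model weights them equally. With true quarterly serial correlation of 0.7 to 0.95, and the working correlation set to the average pairwise value, the variance of the 12-month contrast rises by about 7% to 8% with two pre-start values and 10% to 14% with three.

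**The case against.** Change from baseline is a legitimate endpoint, the trial is sized on the SD of that change, and Sample size allows recalculation after baseline registration. On that view this is a preference. It stands to this extent: nothing here is an error, and the sample size is not at fault.

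Several stronger readings are tempting but not supported.
- A reader might infer that baseline is one noisy reading. The article fixes one extraction time; it does not rule out several values in the look-back, and the full definition may sit in a document not shown.
- A reader might infer that dated earlier values are already in the extract. That is a sound inference but not a statement: a bare count would serve the process score. A 12-month look-back and a third pre-start value are likewise assumptions, because a maximum of 2 points against a quarterly target does not establish the period length.
- A reader might infer that extra pre-start values are free and can never hurt. That is nearly true of separate covariates, which cost a degree of freedom. It is false for the repeated-outcome route (step 8).

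The objection that the range is too wide to be useful has some force. It includes zero, and Background and rationale itself says that regular monitoring in diabetes is hard to sustain, so many patients may have only one value. What the objection does not remove is that the article states a model with no planned baseline adjustment. That is a stated choice, and it can be improved at little cost.

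**Conclusion.** The point holds as a missed efficiency of minor weight. The plan models raw change from one pre-start extraction and adjusts only on imbalance, while its process score requires looking back at earlier HbA1c and blood pressure results.

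Beyond adjustment for a single baseline value, earlier values as covariates would cut residual variance by 0% (pure serial correlation), about 2% to 12% (mixed structures), or 11% to 24% (equal correlations of 0.5 to 0.7). These figures assume two or three pre-start values in every patient and concern patient-level variance, so the realised gain will be smaller. The documents do not allow the range to be narrowed; the baseline extract could.

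**What to change.** 1. State that the baseline extraction keeps the dated HbA1c and blood pressure values from the look-back period already used for the baseline process count.
2. In the mixed models for HbA1c and blood pressure, prespecify two covariates in every analysis, whether or not imbalance is seen: the last pre-start value and the mean of any earlier pre-start values. Where a patient has only one value, use it for both.
3. Do not enter the pre-start values as extra repeated outcomes under the random-intercept model.

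The cost is one covariate beyond the baseline value itself, slightly more data handling, and a few lines of analysis text. No extra patients, visits or tests are needed, and the sample size need not change.

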**Methods:**

The study is a cluster-randomized trial with before/after measurements conducted in Belgian family medicine. Physicians’ practices will be randomly assigned to the intervention or control group in a 1:1 ratio, to receive either the EBMeDS reminders or to follow the usual care process. Randomization will be performed by a statistical consultant with an electronic random list generator, anonymously for the researchers. The follow-up period of the study will be 12 months with interim analysis points at 3, 6 and 9 months. Primary outcome is the one-year pre- to post-implementation change in HbA1c. Patients will not be informed about the intervention. Data analysts will be kept blinded to the allocation.

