### Sample size

Based on the data in the literature, a mean difference of 0.3% in HbA1c change could be considered clinically significant (SD of HbA1c change 1.3%) [23-25]. To detect a mean difference of 0.3% in HbA1c change at four post-treatment occasions, with a two-sided unpaired *t*-test, a 5% family-wise significance level and Bonferroni correction for multiple testing, 1:1 allocation and a power of 80%, a sample size of 463 patients in each group will be necessary, assuming a withdrawal rate of 10%. Additional adjustment for clustering of patients within physician practices by the design effect [26], assuming 10 patients per cluster and an intra-class correlation coefficient of 0.047 based on data in the literature [27], leads to a sample size of 659 patients in each arm. Sample size calculations were based on historical data. They can be adjusted after baseline registrations if correct standard deviations and intra-cluster correlation coefficients are known. Sample size calculation was performed using SAS software.

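### The 0.3% stopping rule can end the trial before its one-year primary outcome exists, and it biases the HbA1c estimate upward when it does

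*Protocol article*

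**What the plan says.** The protocol article, under Primary and secondary outcomes, defines the endpoint: "Primary outcome is the one-year pre- to post-implementation change in HbA1c". The secondary outcomes there are also one-year differences (cholesterol, systolic and diastolic blood pressure), and Table 1 includes process targets counted annually.

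The same section gives the stopping rule: "The trial will be terminated at one of the interim analysis points when a mean difference of 0.3% might be reached" for the HbA1c primary outcome. The Abstract (Methods) fixes when this can happen: "The follow-up period of the study will be 12 months with interim analysis points at 3, 6 and 9 months".

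The Sample size section takes 0.3% as the difference to detect, with an SD of change of 1.3%, tested "at four post-treatment occasions" at a 5% family-wise level with Bonferroni correction. The Data analysis section tests the group difference at each of months 3, 6, 9 and 12 in linear mixed models. Neither section makes a test result a condition for stopping.

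**The concern.** The rule and the endpoint conflict. A difference seen at month 3, 6 or 9 is not the one-year change, yet it can end the trial. The one-year HbA1c comparison and the one-year secondary outcomes are then never observed, and no later analysis can recover them.

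The trigger itself is also badly fixed. It is a raw mean difference, with no standard error, test or direction attached, and the word "might" leaves open whether it is to be observed or predicted. Its value is the effect for which the trial is powered. If that effect is present at a look, the estimate falls above or below the trigger with roughly equal chance. Stopping on a high estimate selects high estimates, so the difference at stopping overstates the truth. If the effect later fades, an early stop would hide that.

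**Working it through.** HbA1c differences are in percentage points; a positive value favours the intervention.

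**Inputs (Sample size section).** Difference 0.3, SD 1.3, two-sided, four tests at 5% family-wise (0.0125 each), power 80%, withdrawal 10%, 10 patients per cluster, ICC 0.047, 659 patients per arm.

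**The plan's own figures.**
- Normal approximation: n = 2 × (1.3 × (2.498 + 0.842) / 0.3)² = 419 per arm; 419 / 0.9 = 466. The noncentral t version gives 421, then 468. The article states 463, so both agree within 3%.
- Design effect: 1 + 9 × 0.047 = 1.423; 463 × 1.423 = 658.8, i.e. 659, as stated.

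**Standard error at a look.** Effective patients per arm: 659 × 0.9 / 1.423 = 417. SE = 1.3 × √(2/417) = 0.090.

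**What the trigger means on that scale.** 0.3 / 0.090 gives z = 3.33, nominal two-sided p = 0.0009. The Bonferroni limit is 2.50 × 0.090 = about 0.225. At planned size the trigger is therefore stricter than the planned tests.

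**Chance of stopping at month 3.** This needs no correlation assumption: 1 − Φ((0.3 − true difference) / 0.090).
- True 0.30: 1 − Φ(0) = 50%.
- True 0.20: 1 − Φ(1.11) = 13%.
- True 0.15: 1 − Φ(1.67) = 5%.
- True 0.075: 1 − Φ(2.50) = 0.6%.

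**Chance of stopping by month 9.** Simulation with 1,000,000 draws per scenario: estimates at the looks are multivariate normal with equal SE 0.090, and the trial stops at the first interim estimate of at least 0.3. The documents do not give the correlation between looks; the ranges below cover 0.3 to 0.9.

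| True difference at months 3, 6, 9, 12 | Stop before month 12 | Mean raw difference at stopping |
|---|---|---|
| 0.30 throughout | 61–80% | 0.36–0.37 |
| 0.20 throughout | 19–31% | about 0.34 |
| 0.15 throughout | 8–13% | about 0.33 |
| 0.15, 0.20, 0.25, 0.30 (builds) | 30–38% | 0.33–0.35 |
| 0.075, 0.15, 0.225, 0.30 (builds) | 20–23% | 0.33–0.35 |
| 0.30, 0.25, 0.20, 0.15 (fades) | 51–63% | about 0.37 |
| 0 throughout | about 0.1% in favour; 0.2–0.3% counting both directions | – |

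At a constant 0.30 the overstatement is 0.36 / 0.30, about 20%. At a constant 0.20 it is 0.34 / 0.20, about 70%. In the fading case the trial would stop at about 0.37 against a one-year truth of 0.15.

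**If the SE is larger than planned.** The trigger stays at 0.3 while its statistical meaning changes. With 300, 200 or 100 patients analysed per arm (same SD and design effect), it corresponds to z = 2.37, 1.93 or 1.37, with nominal p = 0.018, 0.053 or 0.17. At 200 per arm and correlation 0.5, a trial with no effect would stop 6.6% of the time in favour of the intervention and 13% counting both directions.

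**The case against.** Four points on the other side deserve weight.

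**The plan does control multiplicity.** It sizes the trial for four Bonferroni-corrected tests, and at planned size the 0.3 trigger is stricter than that limit. A reader might infer that the rule inflates the false-positive rate. At planned size it does not: null stops are 0.2–0.3%. Higher rates need a larger SE than planned, and nothing in the article says that only part of the information will be available at a look.

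**Frequent early stopping depends on the time course.** The 50% at month 3 requires the full effect to be present by then, which the article does not state. With a gradual build-up to 0.30, the chance before month 12 is 30–38%, or 20–23% with the slower build-up. A reader might infer that the trial would usually stop early. That holds only for effects close to 0.30 from the outset.

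**The reported effect need not be 0.3 or more.** The trigger appears to be a comparison of group means, while the Data analysis section estimates the effect by mixed models, with adjustment for baseline imbalance where needed. The upward bias is real, but a guaranteed floor of 0.3 does not follow.

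**This is a condensed article.** A full protocol or analysis plan may link the rule to a test. That excuses a missing boundary, but not the rule that is stated: even with a significance condition added, a stop at month 3, 6 or 9 would still precede the one-year outcome.

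**Conclusion.** The point stands. The article states a rule that can end the trial before its own primary outcome and one-year secondary outcomes can be measured, on a point estimate that does not scale with precision and is not linked to the planned tests. The damage is loss of the one-year comparison and upward bias in the estimate, not a raised type I error at planned size. That protection is a by-product of the planned SE and disappears if recruitment falls short or the SD or ICC is larger; the Sample size section itself allows that the SD and ICC may be revised after baseline.

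The probabilities rest on an SE of 0.090 at every look, normal estimates, an observed (not predicted) trigger, and an assumed correlation of 0.3 to 0.9. The conflict between rule and endpoint needs none of these assumptions. It should be corrected before the interim data are analysed.

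**What to change.** Delete the termination sentence. Follow all practices to month 12 and base the primary conclusion on the 12-month comparison. Use the month 3, 6 and 9 exports for data-quality and process monitoring and for secondary time-point estimates.

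If an early decision is kept for any reason, state that randomised allocation and HbA1c collection continue to month 12.

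Replacing the trigger with a conventional group-sequential boundary would not be enough. With four equally spaced looks, O'Brien-Fleming limits (z = 4.05, 2.86 and 2.34) correspond to differences of about 0.365, 0.26 and 0.21 at months 3, 6 and 9. The bar would be lower than 0.3 at months 6 and 9. At a true 0.30 and correlation 0.6, stopping before month 12 would rise from 72% to 89%.

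The cost is a one-sentence change and no extra patients. The downside is that control practices may wait up to nine months longer for the reminders.

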### Process evaluation

In the process evaluation, actual use of the system as well as users’ perceptions about the feasibility of the electronic decision support will be measured. These aspects are two necessary components of a process evaluation [22].

Scripts are automatically triggered, and users can see that a script is available from their main screen but have to click to view the script content. As such, click events can give us an indication of physicians’ interest in using the system. A new record is inserted in the log file for each script that is triggered. The following data of actual use are collected in a log file at the physician level: identification code of the script; type of script that is triggered and opened (Reminder, Interaction, Contra-indication, Drugs to avoid, Indication, GuideLine Link); script node expanded (yes/no): *e*.*g*., a long reminder displays when a short reminder is clicked; request for the script information (yes/no).

As such, the percentage and the type of scripts that were opened will be calculated, as well as the percentage of scripts that were expanded and the percentage of scripts for which the script information was requested.

Process information regarding actual use of the Evidence Linker will be logged in a similar way.

